## Abstract

**Background:**

Access to effective smoking cessation programs is crucial to reducing smoking-related morbidity and mortality. Several studies have shown promising results for the application of Acceptance and Commitment Therapy (ACT) in managing psychological or behavioral health problems. However, to date, only one study has examined the feasibility of a telephone-based ACT for smoking cessation and it was conducted among a Western population, in the United States. This study reports a protocol for a randomized controlled trial (RCT) examining the feasibility and potential efficacy of an individual, telephone-delivered ACT for smoking cessation in primary healthcare settings among a Chinese population.

**Methods:**

A randomized, two-group design was chosen, with assessment at baseline (before intervention) and via telephone follow-ups at three and six months. Subjects will be proactively recruited from primary healthcare centers. Eligible participants will be randomized to either the intervention (ACT) or control group following the baseline assessment. Both groups will receive self-help materials on smoking cessation. Those in the ACT group will undergo an initial face-to-face session and two telephone ACT sessions at one week and one month following the first session, to be delivered by a counselor based on the treatment protocol. All of the participants will be contacted by telephone for follow-up assessments at three and six months. Treatment fidelity will be assessed by reviewing around one-fifth of audio-recorded telephone calls.

**Discussion:**

To the best of our knowledge, this protocol describes the first RCT of a telephone-based ACT for smoking cessation. It is also the first RCT of ACT for smoking cessation on a Chinese population. The study will provide us with information about the feasibility of a telephone-delivered ACT within a Chinese sample. If effective, this trial will support the development of ACT treatment protocols that could be made available for use by a greater range of clinicians, and offer an evidence base to support alternative treatments for smoking cessation.

**Trial registration:**

ClinicalTrials.gov ID NCT01652508. Registered on 26^th^ July 2012.

## Background

Smoking is the leading preventable cause of death in the United States [1]. The major causes of excess mortality among smokers are diseases related to smoking, including cancers and respiratory and vascular diseases [1]. Quitting smoking before the age of 40 was found to reduce the risk of dying from smoking-related diseases by about 90% [2]. Access to effective smoking cessation programs is therefore, crucial to reducing smoking-related morbidity and mortality.

Despite the development of a wide and broad range of smoking cessation behavioral interventions that have demonstrated considerable effectiveness [3,4], behavioral interventions reach less than 5% of smokers who try to quit [5], indicating that a more accessible means of intervention is needed. Telephone-based interventions make smoking cessation counseling relatively easily accessible in most countries where telephones are common in most households [6]. Telephone-based counseling has also been found to be an effective intervention for smoking cessation in both the West [7,8] and in Asia [9].

According to a study conducted in Hong Kong among parents who smoke, trained counselors from healthcare settings who proactively recruit smokers to participate in interventions are effective at reaching those who have not yet thought of quitting [10]. Studies in the West have also reported that a proactive telephone approach captures pre-contemplative or infrequent smokers who would not initiate cessation counseling on their own [11,12]. These studies imply that proactive telephone-based smoking cessation interventions may be effective and able to reach a higher proportion of people than a standard reactive approach, in which the smoker initiates a call to a smoking cessation hotline.

### Acceptance and commitment therapy for smoking cessation

A recent innovation in behavioral therapy is Acceptance and Commitment Therapy (ACT) [13]. The focus of ACT is on changing one’s relationship with internal experiences rather than directly changing the content of these experiences, so as to enable more adaptive, flexible, and value-based action. The ACT model is comprised of six core processes that work together to increase psychological flexibility including “acceptance”, “defusion”, “self-as-context”, “the present moment”, “values”, and “committed action”. In adopting ACT for smoking cessation, the acceptance component focuses on helping individuals to recognize and accept internal triggers of smoking, including physical sensations, feelings, and thoughts, without trying to control or avoid these experiences (e.g. craving or withdrawal) of smoking. The commitment component emphasizes the articulation of personal values and making the commitment to take action (i.e. to stop smoking) in alignment with these values [13]. It is expected that this will help smokers to respond flexibly to urges to smoke and lead to adaptive changes in behavior.

ACT has a growing empirical base that demonstrates its efficacy for a wide range of disorders. Recent meta-analyses have found ACT to have effect sizes similar to those in traditional Cognitive Behavioral Therapy (CBT) and superior effects to control conditions, including psychiatric disorders, somatic disorders, and stress [14-16]. Several studies have shown promising results for the application of ACT to smoking cessation when delivered face-to-face to individuals, to a group [17-20], through the web [21] or smart-phone applications [22]. Yet there is only one published trial of telephone-based ACT for smoking cessation, despite previous research showing that telephone-based counseling is a cost-effective intervention for smoking cessation [7]. This telephone-delivered ACT intervention was conducted in the U.S. using a single-arm study that included an average of 3.5 sessions of telephone intervention [21]. Among the 14 participants in the study, a quit rate of 29% at 12-month post-treatment was achieved, which doubled the self-reported quit rate of 12% for standard telephone counseling [9,23]. However, it is not clear whether it is feasible and effective to implement this individual, telephone-based ACT for smoking cessation among a Chinese population, in particular, among people in Hong Kong (HK). Therefore, the aim of this study is to examine the feasibility and potential efficacy of telephone-based ACT for smoking cessation using a proactive recruitment approach by conducting a small-scale randomized control trial (RCT) in HK.

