### Intervention

#### ACT

In addition to the self-help materials on smoking cessation given to the participants in both groups, the participants randomized to the ACT condition will be offered an initial individual face-to-face ACT session at the clinic and two telephone follow-up sessions at one week and one month following the initial session of ACT intervention. Each session will be around 15 to 20 minutes, for a total of approximately one hour over the three sessions. The sessions will be delivered by a counselor experienced in delivering ACT. The intervention will be based on a treatment protocol developed in this study, which is guided by previous ACT for smoking cessation protocols [19] and will incorporate all six core processes of ACT. The first session will mainly help the participants to: (1) accept their cravings and withdrawal symptoms as well as to develop skills for dealing with them without smoking, and (2) identify the values involved in quitting and develop a plan to stop smoking at the initial ACT intervention session. Subsequent sessions will include reinforcing the plan that was developed to quit smoking, supporting participants in continued actions to quit, guided by those identified values, and reinforcing the message on the value of quitting. ACT metaphors/exercises will be used throughout the three sessions. Table 1 provides a session-by-session outline of the intervention.

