**Table 1 Tab1:** **Overview of the ACT sessions**

**Session**	**Format**	**Content**
1	Face-to-face	Clarifying values and barriers
		Identifying and clarifying the intention to cease smoking
		Recognizing “creative hopelessness”
		Two kids in the car metaphor
		The ACT in a nutshell metaphor
		Identifying internal triggers
		Appreciating that “control” is always unworkable
		Encourage participants to practice expansion (exercise 1)
		Dropping anchor (exercise 2)
		Introducing and cultivating mindfulness
		Practicing adaptive responses in the presence of internal triggers
2	Telephone	Brief update and bridge from the first face-to-face intervention
		Willingness as an alternative to control (emotional avoidance)
		Emphasize mindful responses with adaptive behaviors
3	Telephone	Brief update and bridge from the last telephone intervention
		Willingness as an alternative to control (emotional avoidance)
		Emphasize mindful responses with adaptive behaviors

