### Statistical analysis

Statistical analyses will be carried out using the Statistical Package for Social Sciences (SPSS) Statistics v.21 software program. Statistical significance will be considered as p < .05. Descriptive statistics for basic demographics, number of sessions attended by the participants, intervention total length, and per-call duration will be computed. Baseline data will be analyzed to check the comparability of the intervention and control group. The primary analysis is differential changes in the ACT group versus the control group from the baseline to the three-month and six-month follow-up sessions, which will be analyzed within the framework of the Treatment Group. Analyses will be undertaken using mixed-model repeated measures. Primary evidence of the efficacy of ACT will be a significant two-way interaction demonstrating greater change in outcome measures in the ACT group from pre- to post-intervention. An intention-to-treat analysis will be performed. This approach is regarded as the most appropriate method of analyzing RCT data by the highest-quality journals, which have adopted the CONSORT standard [35].

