## Discussion

While research has found that ACT is effective for smoking cessation, no controlled trial studies of telephone-based ACT for smoking cessation has been conducted to date. To the best of our knowledge, this will be the first RCT examining the effectiveness of telephone-based ACT for smoking cessation. It is also the first study that examines the feasibility of the use of telephone-based ACT among a Chinese population.

The results of this study will provide clinicians with the necessary information to develop strategies to help smokers to stop smoking by using a less intense intervention at a time convenient to them. If found to be effective, this therapy can potentially be practiced by a wider range of clinicians than other therapies, given that it is much briefer and readily manualized than existing psychological treatments. It also has the potential to serve as an alternative useful tool for those who do not benefit from other commonly used treatments (e.g. Nicotine-Replacement Therapy, Cognitive Behavioral Therapy). In addition, this proactive recruitment approach may reach service users who might not otherwise be reached using traditional reactive approaches (e.g. Quitline, smoking cessation clinic, etc.). Information on the feasibility of this innovative smoking cessation intervention will provide further insight into its development. If this intervention program is well received by smokers and effective in helping those who smoke to quit, it could be offered to a larger population in Hong Kong or elsewhere at a low cost. It is believed that this telephone-based ACT will, in particular, acceptable to people in HK, as it can save time and allow them time for competing commitments. One anticipated difficulty for the study is subject requirement. However, the plan to establish multiple venues for recruitment with the inclusion of six primary care centers and a longer recruitment period should go some way towards ensuring an adequate participant pool.

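### The aim and planned conclusions name telephone-based ACT, but the tested arm is one clinic session plus two calls, so the trial cannot support a conclusion specific to telephone delivery

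*Protocol article*

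**What the plan says.** **Question and conclusions.** The end of the Background sets the aim as to "examine the feasibility and potential efficacy of telephone-based ACT for smoking cessation using a proactive recruitment approach". It is motivated by a stated gap: "it is not clear whether it is feasible and effective to implement this individual, telephone-based ACT for smoking cessation among a Chinese population". The word 'this' in that sentence points back to a United States study, described as a "single-arm study that included an average of 3.5 sessions of telephone intervention". The Background and Discussion paragraphs of the abstract use telephone-delivered and telephone-based in the same way. The Discussion section says that, to the authors' knowledge, "this will be the first RCT examining the effectiveness of telephone-based ACT for smoking cessation".

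**Tested arm.** The Intervention section says that ACT participants "will be offered an initial individual face-to-face ACT session at the clinic and two telephone follow-up sessions at one week and one month". The Methods paragraph of the abstract and Table 1 agree. Table 1 gives session 1 as face-to-face and sessions 2 and 3 as telephone. The second session opens with "Brief update and bridge from the first face-to-face intervention".

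**Comparator.** Both arms receive the same printed material on quitting, and controls receive nothing else.

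**Feasibility measures.** The Treatment feasibility section lists attendance and retention for the programme as a whole. The Statistical analysis section says that descriptive statistics for "number of sessions attended by the participants, intervention total length, and per-call duration will be computed". Neither section names a measure of uptake for the telephone sessions alone.

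**The concern.** The Background treats mode of delivery as what distinguishes this trial. It lists face-to-face ACT for individual smokers among the approaches with promising results, then points to a single published telephone trial as the reason for a new one. An arm that starts with an individual clinic session falls partly in the category the authors had set aside as already covered.

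What is at stake is what a positive result may be said to show. Reported under the planned wording, a difference between arms would be read as evidence that ACT works when delivered by telephone to Chinese smokers. The same difference would arise if the clinic session did all the work and the calls added nothing. The Discussion's expectation that the programme will be acceptable because it saves participants time also leans on the telephone label, although the programme begins with a counsellor session at the clinic.

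**Working it through.** The plan gives no figure of its own on this point. The check sets the stated question beside the contrast that the design estimates, then measures how much of the package is face-to-face.

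**Step 1. Question against contrast.**

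| Element | Aim and conclusions | Design |
|---|---|---|
| Intervention | Telephone-based or telephone-delivered ACT | One face-to-face session, then calls at one week and one month, plus printed material |
| Comparator | None named in the aim | Printed material alone |
| Precursor cited | Study described only by telephone sessions, average 3.5 | Two telephone sessions |

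There are two arms and one contrast. Write F for the effect of the face-to-face session and T for the added effect of the calls given that session. The contrast estimates F + T. No arm receives the calls without the clinic session, and none receives the clinic session without the calls, so F and T cannot be separated by randomisation.

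**Step 2. Share of the package that is face-to-face.**

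- Sessions: 1 of 3 = 33%.
- Contact time (15 to 20 minutes for every session, from the Intervention section): equal lengths give 1/3 = 33%. The lowest share is 15/(15 + 20 + 20) = 27% and the highest is 20/(20 + 15 + 15) = 40%. The telephone share is therefore about two thirds, with a range of 60% to 73%.
- Content lines in Table 1: 11 in session 1, 3 in session 2 and 3 in session 3. That is 11/(11 + 3 + 3) = 11/17 = 65% face-to-face.

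The two measures point in different directions. By listed content the clinic session carries most of the programme: both named metaphors, both numbered exercises, the values work and the introduction of mindfulness are listed there. Sessions 2 and 3 have nearly identical outlines: an update and bridge, then the same two topics. By time the calls carry most of it.

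**Step 3. Feasibility.** A count of sessions attended does not in general show which sessions they were. A count of two could be the clinic session and one call, or both calls. If everyone attends session 1, calls completed equal the count minus one and telephone uptake can be recovered. If some miss session 1, it cannot be recovered from the count alone.

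**The case against.** The strongest reply is that this is a label that misleads nobody. The blended format is stated in the abstract, the Intervention section and Table 1, so a reader can see what telephone-based covers here. Two of three sessions are by telephone. The aim is modest, since it speaks of potential efficacy in a small-scale trial, and the Discussion's conclusions are conditional on the programme being found effective. The Discussion credits wider reach to proactive recruitment and low cost to the programme as tested, so only the time-saving argument depends on the telephone label.

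Much of this stands, and it rules out several stronger readings that a reader might infer:

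- *That the trial cannot answer its objective.* It can estimate the package's feasibility and its effect against self-help material. Only the telephone-specific claim is out of reach.
- *That the clinic session is the largest part.* That is true of lines in an overview table, not of time. Line counts do not measure dose.
- *That the main ACT content never reaches participants by telephone.* The Intervention section says metaphors and exercises run through all three sessions, and Table 1 gives the calls willingness and mindful responding.
- *That attendance will be overstated.* No section says that attendance will be pooled across sessions and credited to telephone delivery, and call duration is to be described separately.
- *That the self-help control is an error.* It is a disclosed choice and the aim names no comparator. It limits attribution to ACT apart from counsellor contact, but it contradicts nothing.

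What the reply does not remove is the mismatch itself. Disclosure in the methods does not repair an aim and a conclusion that name something else, especially when the Background uses that same distinction to justify the trial.

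**Conclusion.** The point holds in a limited form. The aim and planned conclusions are worded for telephone delivery, while the only contrast estimated is one face-to-face session plus two calls, added to printed material, against printed material alone. The face-to-face share is one third of sessions, about one third of contact time (27% to 40%) and 65% of the content lines in Table 1. Whichever measure is preferred, it is too large to ignore in naming the intervention. A positive result would support the package and could not be credited to telephone delivery.

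This rests on Table 1 and the stated session lengths describing what is delivered. It calls for no change to arms, analysis or sample size. It is a correction to what the trial may conclude, not a finding that the design fails.

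**What to change.** 1. State the aim and conclusion as one face-to-face plus two telephone ACT sessions added to self-help material, versus self-help material alone. Make the same change in the abstract.
2. Qualify the claim to be the first randomised trial of telephone-based ACT, so that it refers to a programme combining a clinic session with telephone follow-up.
3. Report uptake of each of the two telephone sessions separately from session 1, with everyone randomised to ACT as denominator.

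The cost is rewording and one extra tabulation of session attendance, which the plan already intends to describe. The downside is a narrower and less novel claim.

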## Method

### Design

The study will be a prospective, randomized controlled trial involving an intervention and a control group. The participants will be assessed at three time points (i.e. at baseline, three months, and six months post-intervention). The overall design of the study is illustrated in Figure 1. Ethical approval for the study has been obtained by Human Subjects Ethics Application Review Committee of The Hong Kong Polytechnic University.

**Figure 1 Fig1:**
[figure not shown]
**Study design.**

### Participants

#### Selection criteria

Individuals who meet the inclusion criteria will be recruited. The criteria are: (1) aged 18 years or above; (2) have smoke at least one cigarette per day in the past 30 days; (3) not currently undergoing any other smoking cessation program; (4) able to communicate in Cantonese; (5) a Hong Kong resident; (6) currently residing in Hong Kong and expecting to continue for the next six months; and (7) have access to a telephone.

#### Sample size

Sample size calculations were based on the primary outcome of smoking cessation- 7-day point prevalence quit rate. As there has been no study that included a brief ACT for smoking cessation in HK, the sample size estimation was taken reference from available ACT studies for smoking cessation [17-20]. Their pooled effect size (Hedge’s g) was 0.475. The comparisons conditions for ACT in these studies included active treatment (e.g. Nicotine Replacement Therapy, Cognitive Behavioral Therapy); Bupropion; and self-help information with longest 12-month follow-up. According to a smoking cessation study conducted in Hong Kong [9], the 7-day point prevalence quit rate of the control group was 7.4% (i.e. receiving self-help materials). With a significance level of 5% and a power of 90%, under the principle of intention-to-treat analysis, 116 participants will be required for the study.

According to a previous smoking cessation study using a proactive approach [10], around 40% of the smokers who were approached completed the baseline interview on smoking patterns and that 45% of them accepted the invitation to participate in a proactive smoking cessation program. Given that attendance in the community services of the six targeted primary health care centers was 13,000 in the past year and that the prevalence of daily smokers was about 11.1% of the population in 2011 [24], it is estimated that recruiting participants from the six health care centers over a period of seven to eight months can support the required sample size of the study.

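### The stated inputs (g = 0.475, 7.4% control quit rate, 5% significance, 90% power) do not reproduce 116 participants, and the assumed ACT quit rate is not given

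*Protocol article*

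**What the plan says.** The Sample size section sizes the trial on a binary endpoint: "Sample size calculations were based on the primary outcome of smoking cessation- 7-day point prevalence quit rate". It gives two numerical inputs. From earlier ACT cessation studies, "Their pooled effect size (Hedge’s g) was 0.475". From a Hong Kong study, "the 7-day point prevalence quit rate of the control group was 7.4" per cent with self-help materials. The result follows directly: "With a significance level of 5% and a power of 90%, under the principle of intention-to-treat analysis, 116 participants" are needed for the study.

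The section gives no ACT-arm quit rate, no method for turning g into one, no sidedness, no allocation ratio and no allowance for dropout. The Biochemical measures section sets the primary outcome as self-reported seven-day abstinence at a single time point, six months. The Statistical analysis section sets significance at p < .05, again without sidedness.

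**The concern.** The article prints the effect size, control rate, significance level, power and sample size together, so a reader should be able to get from the first four to the fifth. The usual two-group formulas do not get there: 116 is well below the number that g = 0.475 requires at 90% power. The control rate also has no partner, because the quit rate that 116 is meant to detect in the ACT arm is never named.

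The printed power is the probability of detecting the assumed effect. If it is too high, the chance of missing that effect is larger than the 10% the article implies, and a non-significant result could be given more weight than it deserves.

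**Working it through.** **Inputs.** From Sample size: g = 0.475, control rate p1 = 0.074, significance 5%, power 90%, N = 116. Assumed because not stated: 1:1 allocation, so 58 per arm. Two-sided and one-sided tests are both shown. Normal quantiles: 1.960 (two-sided 5%), 1.645 (one-sided 5%), 1.282 (90% power).

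**Attempt to reproduce 116, reading 1: g as a standardised mean difference.**
- n per arm = 2(1.960 + 1.282)² / 0.475² = 93.1, so 94 per arm and 188 in total. One-sided: 75.9, so 76 per arm and 152 in total.
- Power at 58 per arm = Φ(0.475·√(58/2) − 1.960) = Φ(2.558 − 1.960) = 72.5%. One-sided: Φ(2.558 − 1.645) = 81.9%.

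**Reading 2: g as an arcsine effect.**
- p2 = sin²(arcsin√0.074 + 0.475/2) = sin²(0.2755 + 0.2375) = 0.241.
- Pooled two-proportion formula: n = [1.960·√(2p̄(1−p̄)) + 1.282·√(p1(1−p1) + p2(1−p2))]² / (p2 − p1)². With p̄ = 0.157 the two roots are 0.515 and 0.501, so n = 98.0 per arm, 196-198 in total depending on rounding.
- Power at 58 per arm: 69.9% two-sided, 80.1% one-sided.

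**Reading 3: g converted to an odds ratio.**
- ln OR = 0.475·π/√3 = 0.862, so OR = 2.37. Control odds are 0.074/0.926 = 0.0799, ACT odds 0.0799 × 2.37 = 0.189, and p2 = 0.189/1.189 = 0.159.
- The same formula gives 297 per arm, 594 in total (484 one-sided).
- Power at 58 per arm: 29.6% two-sided, 41.3% one-sided.

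| Reading of g | ACT rate | Total N for 90%, two-sided | Power at 58 per arm, two-sided | Power at 58 per arm, one-sided |
|---|---|---|---|---|
| Mean difference | – | 188 | 72.5% | 81.9% |
| Arcsine effect | 24.1% | 196-198 | 69.9% | 80.1% |
| Odds ratio | 15.9% | 594 | 29.6% | 41.3% |

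None of the three readings returns 116 at 90% power, on either sidedness.

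**What 58 per arm does deliver.** Solving the two-proportion power formula for 90%, two-sided, gives p2 = 0.306, about four times 7.4%. One-sided, it gives p2 = 0.278. The Background reports a 29% quit rate for telephone ACT, from a single-arm study of 14 people. For 7.4% vs 29%, power at 58 per arm is 86.4% two-sided and 92.3% one-sided.

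**Is 116 a per-arm figure?** The section says the number is for the study. Its own recruitment figures give 13,000 × 0.111 × 0.40 × 0.45 = 260 a year, or 260 × 7/12 = 152 to 260 × 8/12 = 173 over the planned seven to eight months. That covers 116 but not 232. At 116 per arm, two-sided power would be 95.1%, 94.2% and 52.4% on the three readings, so 90% is not reproduced there either.

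**The case against.** The best defence is that the article condenses a fuller calculation. Several routes do reach about 116, but each needs something the article does not state:

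- One-sided testing at 80% power for 7.4% vs 24.1% gives 57.8 per arm, hence 116. If that is the source, the printed 90% is wrong. The match is suggestive and proves nothing.
- A between-group repeated-measures calculation with three time points and a correlation of about 0.42, or a baseline-adjusted analysis with a correlation of about 0.62, gives about 116 for a continuous outcome. No correlation is given, and the stated basis is a binary quit rate.
- Inflating 93.1 by 20% dropout gives 93.1/0.8 = 116 per arm. No dropout allowance is given, and the per-arm reading conflicts with the text and the recruitment arithmetic.

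What stands is that the true source of 116 cannot be known from the document, so the sponsor should have the chance to show it. It also stands that the trial is described as small-scale and aimed at feasibility and potential efficacy, which limits how much will be built on its power.

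Three stronger readings are tempting and not supported. A reader might infer that power cannot exceed 70-73%, but that assumes two-sided testing, which is not stated. A reader might take the 30% figure as the trial's actual power, but it rests on one conversion among several. A reader might test 7.4% against "the self-reported quit rate of 12% for standard telephone counseling", but the Background offers that rate as a benchmark which telephone ACT exceeded, not as an ACT target.

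**Conclusion.** The stated 90% power does not follow from the stated inputs. With 116 in total and 1:1 allocation, power for an effect of g = 0.475 is about 70-73% two-sided or 80-82% one-sided on the favourable readings, and about 30% or 41% on the odds-ratio reading. The chance of missing the assumed effect is therefore about 18-30% on the favourable readings across both sidedness assumptions, and about 59-70% on the odds-ratio reading, rather than 10%. These are bounds over unstated choices, not a known error rate.

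The 29% reported in the Background is close to the rate that 116 would need. The Sample size section does not say that it was used, and two-sided it still gives about 86%, not 90%. That a null result would in fact be over-read is a possibility, not something the document shows.

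**What to change.** Unless the sponsor can show a different calculation that yields 116, keep the number and correct the statement around it in the Sample size section:

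1. Say that 116 is the total, and give the allocation ratio.
2. Name the test and its sidedness.
3. State how g = 0.475 was converted, and the ACT quit rate assumed.
4. Replace 90% with the power that 58 per arm gives for that rate, or say that 90% (two-sided) holds only for about 30% vs 7.4%.

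If another calculation was used, print its inputs, including any correlation or dropout allowance, so that 116 can be reproduced.

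The cost is a few sentences and probably a lower stated power; no extra participants are needed. Raising N to keep 90% would mean 188 or more in total, above the 152-173 that the section's own recruitment figures project.
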